**Other**
**Hair cortisol and cortisone:** As parameters of long-term endogenous corticosteroid exposure.**Empty canisters:** To study treatment adherence.

### Data management

Data will be stored in an electronic database (Castor EDC) using the participant study number. A master file is available to link the study number with the corresponding patient number at every site. This master file is only accessible for the site investigators. Paper questionnaires and other relevant materials will be safely stored in a locked room. The material will be labelled with a study number, study site, date, and visit number. Data and materials will be monitored every year by an independent monitor.

### Safety

Safety is assured by close monitoring of the subjects using a weekly questionnaire and online diary. Additionally, the use of reliever medication (salbutamol) is monitored to keep track of asthma control. Loss of asthma control is defined as an increase in ACQ score of more than 0.5 points for at least 4 days or progressive dyspnea despite using 500mcg of salbutamol per day by pressurized metered-dose inhaler (pMDI) with spacer. Patients will be asked to contact the coordinating researcher in case of progressive dyspnea despite using ≥ 600mcg salbutamol by pMDI with spacer. A central telephone number (the STOP-telephone) is available for all patients included in this study. As a backup, patients may email (STOP-mail). As a second backup, the local investigators and the general practitioner will be notified of the subject’s study participation and supplied with helpful flowcharts (see Figs. 3 and 4). We aim to follow this procedure before any antibiotics, OCS or ICS are given unless acute treatment is deemed necessary. Patients receive usual care during exacerbation. In case of a second moderate or severe exacerbation (e.g. not related to the first exacerbation), patients are censored and will continue with usual care. It is important to note that patients may choose to stop their participation at any moment, as recommended by the ethical regulations. Study insurance ensures compensation for those who suffer harm from this trial, as regulated by Dutch law (WMO: Medical Research Involving Human Subjects Act) [38].

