### Study procedures

All patients start with a run-in period of 4 weeks using a fixed dose of ICS (Fluticasone 1000mcg/day) as well as salbutamol 100mcg ‘as needed’ (see Fig. 2 and Table 1). This will equalize baseline ICS-exposition. (The period of 4 weeks is similar to earlier tapering studies [15–21]).

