**Fig. 2 Fig2:**
[figure not shown]
**A** Schematic overview of the STOP trial: a 4 week run-in, followed by either an intervention period or a control period of 14 weeks, followed by a crossover. After completion of both treatment periods, patients may choose to participate in the extension study. **B** All patients will be enrolled with a prescription of Fluticasone 1000 mcg and Salbutamol 100 ug (as needed). **C** Patients receive a stable dose of ICS during the control period. **D** During the intervention period, patients half the dose of Fluticasone every 2 weeks. Patients will discontinue ICS after 4 weeks and remain ICS naïve for 10 weeks

**Table 1 Tab1:** Overview of procedures during STOP trial. These procedures will be used in both crossover period 1 and crossover period 2

	Time (weeks)	− 2	0 and 18	4 and 22	6,8,13 and 24,26,31	18 and 36
	Period (1 or 2)	1	1 and 2	1 and 2	1 and 2	1 and 2
	Visit type	Inclusion	Run-in	Baseline	Follow up	Follow up
Activity/Assesment						
Live		x	x	x		x
Telephone					x	
Check inclusion criteria		x				
Informed consent		x				
Medication check		x				
Prior medical history		x				
Comorbidities		x				
Anthropometrics		x		x		x
Exacerbation frequency		x	x	x	x	x
Questionnaires		x	x	x	x	x
Blood samples				x		x
Scalp Hair				x		x
Lung function test*			x	x		x
eNose				x		x
Study information		x	x	x	x	x
Prescriptions			x	x	x	x
SAE form		Thoughout study				

After the run-in period, patients in arm 1 will discontinue ICS (intervention), while patients in arm 2 will continue with a fixed-dose ICS for 14 weeks (control). An abrupt stop of ICS might cause asthma flair-ups. Therefore, ICS-dose will be tapered in two steps (fluticasone 500mcg/daily and 250 mcg/daily) over 4 weeks (see Fig. 1). After those 4 weeks, patients will become ICS-naïve for 10 weeks. Similar studies (which typically had a mix of both T2-high and T2-low patients) used an ICS naïve duration between 20 days and 10 weeks, of which 8 weeks and 10 weeks were most commonly used [15–21]. Empty canisters of salbutamol or fluticasone will be collected and weighed to evaluate protocol adherence.

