The STOP trial is the first to investigate ICS tapering and discontinuation in the population of patients with T2-low asthma and obesity. Several trials on ICS tapering have been published in the past decades [15–21, 51, 55, 56]. However, these trials did not differentiate between T2-high and T2-low asthma. This concludes that ICS cannot be tapered in a mixed population of T2-high and T2-low asthma. However, additional subgroup analysis found that patients with low eosinophil count were more likely to taper and/or discontinue ICS [18, 20, 55]. Later studies, such as Demarche et al., selected patients with low eosinophils and successfully tapering or discontinuing ICS in more than half of these patients. Those encouraging results demonstrated the importance of selection on low blood eosinophils. In addition, recent guidelines usually define the threshold of low blood eosinophils as < 150 cells/µL, whereas earlier trials used thresholds of < 300-400cells/µL. Thus, adhering to the most recent definition of low blood eosinophils may increase the percentage of success.

The primary safety issue regarding this trial consists of patients worsening due to ICS tapering. Based on earlier trials and literature, we estimate the risk of severe exacerbations in patients with obese T2-low asthma as very low in patients with T2-low asthma and obesity [15, 17, 56]. However, to meet safety standards, a detailed plan was created to handle these adverse events.

Current guidelines advocate the use of ICS in all asthma patients. The STOP trial investigates opportunities to taper ICS to zero in patients with obese T2 low asthma. Successful discontinuation of ICS will lead to decreased exposure to glucocorticosteroids. On the contrary, failed ICS tapering justifies exposure to glucocorticosteroids in this patients group, as benefits appear to outweigh risks. Either way, the outcomes of this trial are expected to influence future guidelines on T2 low asthma and obesity.

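### The reliever dose at which patients are asked to call (600 mcg or more, no period given in the prose) can sit above the dose that already defines loss of asthma control (500 mcg per day)

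*Protocol article*

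**What the plan says.** The Safety section of the protocol article gives two rules in adjacent sentences.

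- **Definition of loss of asthma control.** There are two alternative limbs: a rise in ACQ of more than 0.5 points lasting at least 4 days, or "progressive dyspnea despite using 500mcg of salbutamol per day", taken by pMDI with spacer.
- **Instruction to the patient.** "Patients will be asked to contact the coordinating researcher in case of progressive dyspnea", the dose here being at least "600mcg salbutamol by pMDI with spacer". The sentence does not say whether this is per day, per episode or over some other period.

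The same section states the aim of the contact procedure: "We aim to follow this procedure before any antibiotics, OCS or ICS are given", unless acute treatment is deemed necessary. It also describes monitoring that does not depend on a call at this dose: follow-up "using a weekly questionnaire and online diary", tracking of reliever use, and a study telephone line open to all participants, with email as backup.

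The reliever is described in Study procedures ("as well as salbutamol 100mcg", as needed) and in the Fig. 2 legend ("Salbutamol 100 ug (as needed"). The Discussion states: "The primary safety issue regarding this trial consists of patients worsening due to ICS tapering".

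**The concern.** The two sentences describe the same symptom and the same device but give different doses, and the text does not explain the difference. An instruction that brings a worsening patient to the team's attention should apply no later than the event it is meant to detect. On the plain per-day reading it applies later: progressive dyspnea at 500 mcg per day is already loss of control, yet the request to call starts at 600 mcg.

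What is at stake is safety handling. Patients go without ICS for 10 weeks in the intervention period, and Table 1 lists telephone contacts, not live visits, between the baseline and final visits of each period. The patient's call is one way into the procedure that the team wants followed before other treatment is given. A dose trigger without a period can also be applied differently by patients, local investigators and general practitioners.

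**Working it through.** No statistical figure is involved, so the check sets the two rules side by side under each reasonable reading.

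**Inputs**

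- Definition: 500 mcg per day (Safety).
- Call trigger: 600 mcg or more, no period in the prose (Safety).
- Dose step: 100 mcg. This is an assumption, taken from the reliever strength in Study procedures and the Fig. 2 legend.

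**Step 1. Both doses per day.** In doses of 100 mcg, 500/100 = 5 and 600/100 = 6. For a patient with progressive dyspnea:

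| Doses per day | mcg per day | Definition met, if it means 500 or more | Definition met, if it means more than 500 | Asked to call (600 or more) |
|---|---|---|---|---|
| 4 | 400 | no | no | no |
| 5 | 500 | **yes** | no | **no** |
| 6 | 600 | yes | yes | yes |
| 7 | 700 | yes | yes | yes |

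- Definition read as 500 or more: the rules disagree at one level, 5 doses. The gap is 600 − 500 = 100 mcg, which is one dose, and 600/500 = 1.20, or 20%.
- Definition read as more than 500: the rules agree at every whole dose and the gap is zero. The text does not say more than, although the next sentence does use an explicit greater-or-equal sign.

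**Step 2. 600 mcg as a rescue dose for one episode.** A daily total and a single-episode dose are on different scales, so no gap in doses can be stated and the 1.20 ratio does not apply. As an illustration, six separate doses over a day give 6 × 100 = 600 mcg. With progressive dyspnea that meets the daily definition, but no single episode need have reached 600 mcg.

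**Summary of readings**

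| Reading | Distance between the two rules |
|---|---|
| Both daily, definition includes 500 mcg | 100 mcg (one dose, 20%) |
| Both daily, definition means more than 500 mcg | none |
| 600 mcg per episode | not comparable |

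The prose needs a clarification under each reading: of the number, of the period, or of both.

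**The case against.** The strongest reply is that the mismatch depends on the reading. If 500 mcg has been used and has failed, the next whole dose is 600 mcg, and the call then follows directly from the definition. If 600 mcg is an acute rescue dose, converting it to a daily dose would change a clinical instruction, and the text does not justify that. Both points stand, which is why the fix below does not force a per-day conversion.

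Fig. 3, the flowchart for progressive dyspnea, is not shown and may give the period. This also stands: the missing period is established for the prose alone. The difference between 500 and 600 mcg in the prose does not depend on the figure.

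A reader might infer that patients may call only at 600 mcg, or that a patient below that dose goes unnoticed. The documents do not support either. Nothing forbids an earlier call and the study telephone is open to all participants. The weekly questionnaire, the diary and reliever monitoring run in parallel, and Table 1 adds telephone contacts at weeks 6, 8, 13 and 24, 26, 31. The ACQ limb of the definition needs no salbutamol threshold.

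It can also be said that a definition and an action trigger need not share one number. That is true, but a trigger set above its own event, with no reason given, is hard to defend when aligning the two costs almost nothing.

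**Conclusion.** The point holds as a minor correction to safety wording. The prose states two reliever thresholds for the same symptom, and the one that prompts the patient to call is the higher. The size is one dose of 100 mcg per day (20%) if both are daily and the definition includes 500 mcg, zero if the definition means more than 500 mcg, and not quantifiable if 600 mcg is per episode. The dose count assumes 100 mcg per dose.

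A reader might go further and infer an effect on the trial's results. The article does not support that. It does not use loss of asthma control as an endpoint. Censoring follows a second moderate or severe exacerbation, and the DSMB may investigate when 12 or more exacerbations have occurred. The primary endpoint, its test, the sample size and the grading of exacerbations are untouched. The reason to act is that the thresholds bear on what the Discussion itself calls the primary safety issue.

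**What to change.** Set the call trigger no higher than the definition of loss of control, and give its period. Any one of these would do:

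1. Ask patients to call in case of progressive dyspnea despite 500 mcg salbutamol per day or more.
2. If the clinical team prefers the higher dose, write the definition as 600 mcg per day or more and state the call trigger per day as well.
3. If 600 mcg is meant as a rescue dose for a single episode, say so, keep it, and add a separate call instruction at the daily threshold in the definition.

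Carry the choice into the patient instructions and flowcharts where they differ. The cost is a wording change in the Safety section and possibly a few more calls to the study telephone.

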## Methods

### Study design

The STOP trial is initiated by the ‘STZ center of Excellence for Asthma and COPD’ of the Franciscus Gasthuis & Vlietland hospital, collaborating with the Maasstad hospital and the Albert Schweitzer hospital. This multicenter approach ensures a larger number of possible study subjects and decreases selection bias due to social-economical differences between regions of Rotterdam. Patients will be randomized into one of two study groups to avoid allocation bias. Both groups consist of a control period and an intervention period in a 2 × 2 crossover pattern that creates balanced groups maximizes statistical power, and allows for analysing a possible sequence effect. The study has a non-inferiority design, which tests the hypothesis that ICS tapering is not inferior to ICS continuation. This intervention trial has an open-label to determine the effects of ICS tapering in a real-life situation.

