## Sample size and statistical analysis

### Sample size calculation

The primary endpoint is the mean difference in ACQ score between the intervention period and the control period whit correction for the baseline ACQ score. This will be tested using a paired t-test for within-subjects designs, with a one-sided alpha of 0.05, a beta of 0.10, a rho of 0.5, a non-inferiority margin of 5% (0.25 ACQ points), an allowable difference (a minimal clinically important difference) of 0.5 ACQ points and a drop-out rate of 10%. The population variance $${\upsigma }_{\mathrm{e }}^{2}$$ was calculated using a real live cohort of patients in the Franciscus Gasthuis & Vlietland. This cohort included all new referrals at the outpatient clinic with a suspicion of asthma. This cohort (n = 52) was selected for having a BMI ≥ 30, blood eosinophils ≤ 0.15 cells/µl, clinically proven asthma, and no obstructive lung diseases otherwise. All patients filled in an ACQ at baseline and 6 months, after which the difference $${ACQ}_{endpoint}- {ACQ}_{baseline}$$ was calculated for every patient. This resulted in a mean of − 0.2749 with a variance 0.7847. A sample size of 120 patients was calculated using the formulae in Fig. 5.

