### Statistical analysis

Study data will be analysed according to the intention-to-treat approach. Results of the statistical analysis consist of descriptive univariable and multivariable analysis. Continuous parameters with (approximately) normal distributions will be summarized with means and SDs (or 95% CIs). Continuous primary study parameters with skewed distributions will be summarized with medians and interquartile ranges (IQR). Finally, nominal and ordinal primary study parameters will be summarized with numbers (percentages).**Primary study parameter**

The primary endpoint is defined as the difference in ACQ between the intervention period and control period relative to the baseline ACQ score. Definitions:Baseline: ACQ score at the first visit of period 1 or period 2Endpoint: ACQ at last visit of period 1 or period 2

The non-inferiority margin is 5% (i.e., 0.25 out of a maximum of 5 ACQ points). Non-inferiority will be established if the lower limit of a one-sided 95% confidence interval for the mean difference in ACQ score between the intervention period and control period is within the absolute 5% non-inferiority margin of the mean in the control arm.2.Secondary study parameter(s)

The time to first exacerbation will be tested with Kaplan–Meier curves and log-rank tests to estimate the effect over time for both patient groups. Next, Cox regression will be used to measure the treatment effect adjusted for BMI and hospital as fixed covariates.

The majority of secondary variables are continuous and will be described by descriptive compared between intervention group and control group.

The change in time of several secondary parameters will be estimated by repeated measurements analysis. Linear mixed modeling will be used for continuous variables. Generalized estimated equations for binary data with logit link function will be used for the categorical variables.3.Interim analysis

No interim analysis has been planned to prevent alpha loss. An independent Data Safety Monitoring Board (DSMB) may conduct an investigation of adverse events when ≥ 12 exacerbations may have occurred.

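### The rule that censors patients after a second exacerbation is undefined for the paired ACQ comparison, conflicts with intention-to-treat, and can favour non-inferiority if such events cluster on withdrawal

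*Protocol article*

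**What the plan says.** Four statements in the protocol article bear on this point.

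- **Study design:** "The study has a non-inferiority design, which tests the hypothesis that ICS tapering is not inferior to ICS continuation".
- **Sample size calculation**, on the primary endpoint: "This will be tested using a paired t-test for within-subjects designs". The Statistical analysis section defines the endpoint as the ACQ at the last visit of each period, taken relative to that period's baseline.
- **Statistical analysis:** "Study data will be analysed according to the intention-to-treat approach". No other analysis set is named.
- **Safety:** "Patients receive usual care during exacerbation". The same section foresees that antibiotics, OCS or ICS may be given. After a second moderate or severe exacerbation unrelated to the first, "patients are censored and will continue with usual care". The rule is not limited to the withdrawal period.

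The only time-to-event analysis described is of time to the first exacerbation.

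**The concern.** Censoring belongs to time-to-event analysis. A paired mean difference either has both period values for a patient or it does not. The word cannot refer to the planned survival analysis either: that analysis ends at the first exacerbation, which has already happened when the rule applies. The natural reading is that the patient leaves trial follow-up. A patient who leaves in period 1 has no period 2 value, and one who leaves in period 2 has no period 2 endpoint. In both cases a paired t-test cannot use the patient.

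The trigger is itself a poor outcome, so this would be exclusion based on response, which intention-to-treat is meant to prevent. In a non-inferiority trial, losing more patients who did badly on withdrawal than on control moves the estimate towards the desired conclusion. The stake is a false finding that control is maintained without ICS.

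**Working it through.** **Inputs from the article (Sample size calculation).** One-sided alpha 0.05, beta 0.10, rho 0.5, margin 0.25 ACQ points, variance of ACQ change 0.7847, drop-out 10%, N = 120.

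**Step 1: reproduce the plan's figure.**
- Variance of the within-patient difference = 2 × 0.7847 × (1 − 0.5) = 0.7847.
- n = 0.7847 × (1.645 + 1.282)² / 0.25² = 107.5, so 108.
- 108 / 0.9 = 120, which matches.

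The sample size is not in dispute, and the same variance is used below. The 10% allowance replaces lost precision. It does not correct a bias from who is lost.

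**Step 2: assumptions that are not in the article.** Taken over all 120 patients, the true difference (withdrawal minus control, higher is worse) equals the margin, 0.25. A share f fails on withdrawal with an excess of D = 1.0 ACQ point, and none fail on control. Failures' pairs are dropped and all other data are complete. Non-inferiority is declared when the upper one-sided 95% limit of the difference is below 0.25.

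**Step 3: effect of dropping failures.**
- Mean among retained pairs = 0.25 − f × D
- Retained pairs n = 120 × (1 − f)
- P(declare non-inferior) = Φ[ f × D / √(0.7847/n) − 1.645 ]

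| f | n | retained mean | standard error | P(false non-inferiority) |
|---|---|---|---|---|
| 0 | 120 | 0.25 | 0.081 | Φ(−1.645) = 5% |
| 5% | 114 | 0.20 | 0.083 | Φ(0.603 − 1.645) = 15% |
| 10% | 108 | 0.15 | 0.085 | Φ(1.173 − 1.645) = 32% |

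**Step 4: dependence on where failures occur.** This is a simulation with 10,000 trials per setting, D = 1.0, the true all-patient difference held at 0.25, and failures in either period dropped.

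| failures on withdrawal / control | mean among retained pairs | P(false non-inferiority) |
|---|---|---|
| 10% / 5% | 0.20 | about 14% |
| 10% / 10% | 0.25 | 5% |
| 5% / 10% | 0.30 | about 1% |

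The direction depends on the imbalance between periods, not on the rule alone.

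**Step 5: patients kept and scored after rescue.** Suppose failures occur only on withdrawal, stay in the analysis, and rescue has removed half of D by the last visit. The mean is then 0.25 − f × 0.5, that is 0.225 at f = 5% and 0.20 at f = 10%. With n = 120 the chance of declaring non-inferiority is about 9% and 15%. This measures the distance from the effect that would have been seen without rescue. It is not an error in a treatment-policy estimate.

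**Step 6: plausibility of f.** Each censored patient needs at least two qualifying exacerbations. At f = 5% that is 6 patients and at least 12 events. At f = 10% it is 12 patients and at least 24 events. The article lets the DSMB investigate at 12 or more exacerbations and expects severe ones to be very rare. It gives no rate for moderate ones.

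**The case against.** The strongest reply is that the article nowhere says a censored patient's ACQ is excluded. The paired t-test is named under the sample size, the analysis section adopts intention-to-treat, and *censored* could mean that study treatment stops while follow-up continues. Handling of missing values is commonly left to the analysis plan, which is not shown. This stands as far as it goes: loss of the pair is an inference. It does not remove the conflict, because the article states a rule that has no defined meaning for its primary comparison and whose plain reading contradicts its stated analysis principle.

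A reader might also infer that every patient who fails withdrawal is either removed or hidden by rescue, so that the result must lean towards non-inferiority. The documents do not support that:

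- Censoring needs a second exacerbation and applies in both periods. A patient whose ACQ worsens without rescue is still scored at the last visit, against withdrawal.
- The bias requires more such events on withdrawal than on control.
- Scoring after rescue is a legitimate treatment-policy value in a trial whose stated aim is the effect in real life. The rescue flowcharts (Figs. 3 and 4) are not shown.
- A per-protocol or supportive analysis may be in the full protocol or analysis plan, so its absence here is not a finding.

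Large figures should be resisted too. With f = 20% and an excess of 1.25, the true effect is 0.25, and the 96 remaining pairs give Φ(0.25/√(0.7847/96) − 1.645) = 87% instead of 5%. If censoring is the route, that needs 24 patients and at least 48 exacerbations, which sits badly with the article's own expectations.

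**Conclusion.** The point holds in limited form. The censoring rule is undefined for the paired last-visit ACQ comparison. If it means leaving follow-up, it conflicts with intention-to-treat by excluding patients because of their outcome. The bias favours non-inferiority when these events are more frequent on withdrawal. That is the expected pattern if withdrawal is harmful, and so the case in which the type I error matters. With equal rates there is no bias, and with more events on control it reverses.

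The size cannot be derived from the article. The 15% and 32% figures rest on an assumed 1.0-point excess, failures on withdrawal only, complete loss of their pairs, and assumed shares of 5% and 10%. They show that a few lost patients can matter, and they are not a forecast.

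**What to change.** 1. In the Safety section, replace the censoring statement with one saying that ACQ-5 collection continues at all scheduled visits after the event and that the patient stays in the primary intention-to-treat analysis. Treatment of the patient is unaffected.
2. Analyse the primary endpoint with a linear mixed model, already planned for continuous secondary variables, so that patients with an incomplete pair still contribute. The model does not by itself repair outcome-dependent loss beyond what the observed data explain, so step 1 is the essential part.
3. Add a supportive sensitivity analysis that does not count rescued patients as controlled without ICS, for example by using their last ACQ before rescue. Report it beside the primary result. Making it a second condition for the non-inferiority claim would be a trade-off and is not needed to resolve this conflict.

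The cost is a wording change, some further follow-up of the patients concerned, one extra analysis, and a slightly harder non-inferiority claim. Table 1 already schedules questionnaires at every visit. The Safety section's weekly questionnaire is not named as the ACQ-5, so it should not be assumed to supply the missing values.
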